# A series of N-of-1 trials to assess the therapeutic interchangeability of two enalapril formulations in the treatment of hypertension in Addis Ababa, Ethiopia: study protocol for a randomized controlled trial

**DOI:** 10.1186/s13063-017-2212-0

**Published:** 2017-10-10

**Keywords:** Hypertension, Enalapril, Therapeutic equivalence, N-of-1 trial, Randomized controlled trial, Generic

## Abstract

**Background:**

Hypertension is one of the leading causes of morbidity and mortality in Ethiopia. Treatment usually involves lifelong medication use. Enalapril is a common drug for the treatment of hypertension in Ethiopia. However, the drug is expensive and, therefore, there is limited capacity for people to afford the treatment. Locally produced Enalapril is a cost-effective solution to treat the disease. However, as local medicines regulation does not include bioequivalence tests on locally produced drugs, physicians and patients need assurance about the effectiveness and safety of local generics. Evidence on therapeutic equivalence is needed on these untested local drugs.

**Methods:**

This is a hospital-based, randomized, partially blinded, three-cycle crossover trial in single patients, comparing a locally produced version of enalapril with enalapril imported from Europe. Patients involved in this trial are not blinded, as there is no local facility to produce relatively small numbers of placebos or encapsulated drugs. To ensure blinding of study investigators and data analysts, study medications are prepared by an independent pharmacy unit using opaque medication packaging. The importance of maintaining blinding is also part of patient pre-trial education. Each N-of-1 trial will consist of three successive 14-day treatment pairs, each pair comprising 7 days of 5–20 mg local and 7 days of 5–20 mg imported enalapril taken once daily in the morning. The primary outcome will be the average difference in systolic blood pressure as measured by home blood pressure measurements.

**Discussion:**

The number of locally produced products, such as enalapril, being approved without proof of bioequivalence is dramatically increasing. By bridging the information gap on bioequivalence, the trial will give rigorous evidence on therapeutic equivalence of locally produced enalapril in the treatment of hypertension. If there is no difference, the hypothesized result, then patients can take the local medicine with confidence. This trial will also will determine whether aggregated N-of-1 studies are feasible to evaluate untested generic drugs in resource-limited countries where bioequivalence testing centers are unavailable.

**Trial registration number:**

Australian and New Zealand Clinical Trial Registry, ID: ACTRN12616001088437p. Registered on 12 August 2016.

**Electronic supplementary material:**

The online version of this article (doi:10.1186/s13063-017-2212-0) contains supplementary material, which is available to authorized users.

## Background

Ethiopia is the second most populous country in Africa with a population size of 100,936,943 [1]. In 2011, the World Health Organization (WHO) estimated that 34% of the Ethiopian population dies from non-communicable diseases, with a national cardiovascular disease prevalence of 15% [2]. In particular, hypertension is a major public health challenge because of its high frequency and associated risks. Ethiopian studies have found a significantly high prevalence of hypertension at the workplace (27.3%) [3] and in an urban community (30%) [4]. In 2008, the Ethiopian Federal Ministry of Health (FMOH) identified hypertension as the seventh leading cause of mortality [5]. This makes it the single most important cause of mortality from non-communicable diseases in Ethiopia.

Drug therapy for hypertension involves the use of a series of drug classes and often requires taking multiple drugs, which makes the treatment expensive for patients. In order to provide better access to affordable drugs, the Ethiopian Government legalized the production and commercialization of locally produced generic drugs. Because of their lower cost, the use of generic drugs is supported by health care systems which recommend that physicians prescribe them, rather than brand-name drugs [6–8]. Therefore, treatment of hypertension with generics is an ideal option to reduce health care costs and improve therapeutic compliance in Ethiopia.

### Lack of accredited bioequivalence center in Ethiopia

In most places in the world, an application for marketing approval of a new generic product must reference a corresponding product, which was approved on the basis of clinical trials to support claims of safety and efficacy. This means that generics must show bioequivalence (BE) to a reference product and this is accepted by the European Union (EU) [9], the United States of America (USA) [10] and the WHO [11]. However, due to the lack of a bioequivalence testing center in Ethiopia, whether locally produced drugs are therapeutically equivalent, and thus interchangeable with the originally marketed products, is not known.

One practical example for this, occurred when the Ethiopian medicines authority announced that the production of one particular locally manufactured drug was banned when it received claims of ineffectiveness of the drug from various health professionals [12]. Several studies have also reported high levels of negative perceptions regarding generic drugs among health professionals and patients in Ethiopia [13, 14].

### Enalapril

Enalapril is an angiotensin-converting enzyme (ACE) inhibitor used in the treatment of hypertension, symptomatic heart failure and asymptomatic left ventricular dysfunction [15]. Onset of antihypertensive activity is at 1 h, with peak reduction of blood pressure (BP) achieved by 4–6 h after administration. The extent of absorption of enalapril from enalapril tablets administered per os is approximately 60%. The effective half-life for accumulation of enalapril following multiple doses of the drug is 11 h. It is metabolized in the liver and excretion is primarily renal [16]. One study demonstrated that the first dose of enalapril was effective and produced effects similar to those measured after 7 days, and after 1 month of treatment [17]. In Ethiopia, enalapril is commonly used to treat hypertension and is one of the first-line treatment options in the routine management of patients with hypertension [18].

### What are N-of-1 trials?

N-of-1 tests are double-blinded, multiple-crossover, comparative trials of effect. They are indicated whenever there is substantial uncertainty regarding the comparative effectiveness of different treatments being considered for an individual patient. Guidelines commissioned by the US Department of Health and Human Services, and a recently published book have both documented the use of N-of-1 tests as a means of formally assessing the bioequivalence of generic drugs [19, 20]. Researchers have used N-of-1 tests to prove therapeutic interchangeability of generic warfarin [21] and nifedipine [22]. An N-of-1 trial also concluded that follow-up of hypertension using home BP measurement is possible [23].

N-of-1 trials are suitable in the following conditions: stable or chronic conditions; treatments that have a rapid onset and offset of effect, and a short half-life resulting in minimal washout periods [24, 25].. Enalapril meets all the conditions of a treatment that is amenable to N-of-1 trials [23].

### Justification for the trial

High-quality clinical evidence is required to prove the comparative efficacy and safety of locally produced enalapril compared with an accepted comparator, without a bioequivalence profile being present. Though they are cheap, people distrust local drugs. Pharmacodynamic (PD) endpoint bioequivalence studies can be used to establish bioequivalence of drug products when pharmacokinetic (PK) data is not possible [26, 27]. Compared with clinical endpoint bioequivalence studies, PD studies are more cost-effective, sensitive and less complicated methods for detecting drug formulation differences. Conducting classical clinical trials is difficult in Ethiopia. N-of-1 trials are relatively easy to conduct and generate results for each person. N-of-1 trials are not common in Africa. In particular, there are no published reports of N-of-1 methodology being used to assess the therapeutic equivalence (TE) of a product without a bioequivalence profile against another medicine that has a bioequivalence profile. If the tests prove feasible and acceptable, they can provide a bridge between the less rigorous regulatory environment in many resource-poor countries, and one in the future where bioequivalence tests are the norm.

N-of-1 tests prove TE and interchangeability in individual patients. Furthermore, when N-of-1 tests from multiple individuals are aggregated (aggregated N-of-1 tests), a smaller sample size is required to produce generalizable data compared to parallel randomized controlled trials (RCTs) [22, 28]. Therefore, as a proxy measure to a bioequivalence study, the aggregation of a modest number of patients who are undergoing N-of-1 tests could be used to determine overall TE in the population. To inform the design of this study, we conducted a preliminary qualitative study to assess the views of patients and physicians on local drugs. (publication in process) We identified that participants preferred imported drugs from Western countries, particularly Germany. For this reason, the German version of enalapril has been chosen as a comparator drug for this trial.

### Objectives

The objectives of the trial are to:Compare the TE of locally produced enalapril and the German version of enalapril using N-of-1 TE tests (both versions are registered to treat hypertension in Ethiopia)Assess whether N-of-1 TE tests are feasible to generate bioequivalence information for generic drugs in resource-poor settings

## Methods

### Trial design

This is a TE study using N-of-1 trials or tests. Each N-of-1 test will be a randomized, partially blind, multiple-crossover study designed to simulate the routine clinical practice of switching a patient between generic and brand forms of enalapril.

Each N-of-1 trial will consist of three successive 14-day treatment pairs, each pair comprising 7 days of Envas and 7 days of Ena-Denk in random order, taken once daily in the morning. The order of treatments in each treatment pair will be determined by block randomization. Figure 1 shows the study design for a sample arrangement of treatment order. The protocol conforms to the Standard Protocol Items: Recommendations for Interventional Trials (SPIRIT) guidelines [29]. The SPIRIT Checklist can be found in Additional file 1. Figure 2 shows the SPIRIT schedule of enrollment, interventions and assessments [29].

**Fig. 1 Fig1:**
[figure not shown]
Diagram of N-of-1 test for treatment of hypertension using two enalapril formulations

**Fig. 2 Fig2:**
[figure not shown]
Standard Protocol Items: Recommendations for Interventional Trials (SPIRIT) schedule of enrollment, interventions and assessments

Blood pressure will be assessed morning and evening during the period, and by a study clinician at the end of each 7-day period. Blood pressure measurements taken in the first 2 days of each period will be discarded during the analysis stage to allow for washout.

### Study setting

This is a single-site, hospital-based study that will be conducted in the AHRI/ALERT center, one of the government-owned institutes located in the capital city of Ethiopia (Addis Ababa). The complex comprises the All Africa Leprosy, Tuberculosis and Rehabilitation Training Center (ALERT) specialized hospital and the Armauer Hanson Research Institute (AHRI).

### Study participants

Participants who fulfill the following inclusion criteria: (1) male and female patients with primary hypertension controlled on enalapril alone or an enalapril-containing regimen, and who have achieved a BP target of 140/90 mmHg or less in at least the last 2 months (clinic readings), (2) the enalapril dose is between 5 mg and 20 mg daily, (3) aged between 18 and 80 years, (4) serum electrolyte and creatinine within the normal range (or the clinical investigator considers the deviation to be irrelevant for the purpose of the study) and (5) a normal electrocardiogram (ECG) or stable abnormalities which the clinical investigator does not consider a disqualification for participation in the study.

Exclusion criteria include: (1) any evidence of clinically significant, poorly controlled hematologic, renal, hepatic, gastrointestinal, or diabetic problems, (2) any evidence within the last 6 months of clinically significant diseases involving the cerebrovascular, autoimmune, or cardiovascular systems, including poorly controlled angina pectoris, secondary hypertension, congestive heart failure, myocardial infarction or stroke, (3) concomitant use of major psychotropic agents or antidepressant drugs or regular use of non-steroidal anti-inflammatory agents, high-dose aspirin, or any agent that could raise or lower BP within the last 2 months, (4) a history of drug or alcohol abuse, (5) sensitivity to ACE inhibitors and (6) pregnant (positive pregnancy test) or breast-feeding women or women who are planning to become pregnant during the trial period.

## Interventions

### Investigational products

This N-of-1 TE study will compare two formulations of enalapril (Envas and Ena-Denk); see Table 1.

**Table 1 Tab1:** Identity of investigational products

Description	Test product	Reference product
Name	Envas	Ena-Denk
Drug substance	Enalapril	Enalapril
Administration	Per oral	Per oral
Formulation	Tablet	Tablet
Dose	5–20 mg	5–20 mg
Manufactured by	Cadila Pharmaceuticals Ltd., Ethiopia	Denk Pharma, German

### Enalapril

For each patient, individualized enalapril will be prescribed for the duration of the study (6 weeks). Drugs will be bought from a well-regulated wholesale pharmacy. Study medications will be packed and labeled by an independent pharmacy unit in six opaque bottles containing 1 week’s supply of medicines each, and randomly ordered.

### Randomization

We will use block randomization, and with a block size of 2, by a statistician at The University of Queensland (UQ). The order in which patients receive drugs will be randomized by computer for each single case, such as BA-AB-BA or AB-BA-BA. The randomization schedule will be sent to a pharmacist who is independent of the study at the ALERT hospital. Prepared study medications will be delivered, stored and dispensed at the AHRI pharmacy unit. Randomization codes will be kept by the ALERT pharmacy. The codes will be broken by the Data Safety and Monitoring Board (DSMB) if safety concerns arise. Figure 3 shows the flow of participants through the trial.

**Fig. 3 Fig3:**
[figure not shown]
Flow of participants through the study. * This washout period is an analytic washout period. Blood pressure measurements taken in the first 2 days of each period will be discarded during the analysis stage to allow for washout

### Blinding

Due to lack of encapsulation machines or matching placebo tablets locally, this N-of-1 study is planned to be a partially blinded trial. Patients may identify the physical differences between the two drugs, but will not know the identity of the medicines that they are taking unless the enalapril that they are currently prescribed is one of the test agents. This is possible but unlikely. However, the trial staff will remain blinded as study medications are prepared by a pharmacist who is independent of the trial. The importance of maintaining blinding is emphasized in the patient education that is a routine part of patient preparation for participation in the trial.

### Selection of doses in the study

Participants in this study are those whose BP is currently controlled with a regimen including enalapril 5–20 mg. They will continue on their current dose for the duration of the trial.

### Dose adjustment plan for uncontrolled BP

Standard clinic BP measurement is made at the end of each 1-week treatment period. Patients included in the study are those whose BP is controlled at the current dose and form of enalapril which they are taking. If a patient’s BP becomes less well-controlled, the dose of enalapril will be adjusted according to a preplanned protocol (see Table 2).

**Table 2 Tab2:** Dose adjustment plan

Change in average BP	Initial dose	Dose adjustment	Maximum
< + 5 mmHg	Current dose	No adjustment – complete the cycle	20 mg
≥ + 5 mmHg	Current dose	Current dose + 5 mg	25 mg
≤ 5 mmHg fall	Current dose	No adjustment – complete the cycle	20 mg
≥ 5 mmHg fall and asymptomatic	Current dose	No adjustment – complete the cycle	20 mg
≥ − 5 mmHg and symptomatic	Current dose	Current dose − 5 mg	15 mg

*BP* blood pressure

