### Study withdrawal or interruption

If a concomitant medication has to be taken that might influence BP, that person will cease the trial until the new medicine has ceased or the dose has been stable for at least 2 weeks. If they wish, the participant can restart the study, substituting a new randomly packed cycle of medicines for the interrupted cycle. Unused medicines from the trial will be discarded. If the person has to continue on the new medicine, the trial will cease, and the data collected will be analyzed if at least one cycle has been completed.

Participants will also be withdrawn from the study under the following conditions:Patient request, patient non-compliance, or the development of an exclusion criterionIf, in the opinion of the treating clinician, the patient’s interests are best served by withdrawing from the trial

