### Data analysis and study result report

#### Individual study result report

At the end of the trial, BP measurements will be analyzed and the result will be given to the treating physician. After looking at these results, the patient and the treating physician will be able to decide if the local drug works for treating the patient’s hypertension.

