#### Statistical methods

Analysis will be conducted based on BP measurements taken in the last 5 days of each of the six periods. The first 2 days’ BP measurements in each period will be discarded. Based on the academic literature [33], 6 mmHg is accepted as the MCID. Therefore, a SBP difference of ≥ 5 is considered clinically significant. A mean change in evening SBP of < 5 mmHg between the two test medicines in at least two treatment cycles will be considered as representing TE.

Differences in treatment means will be explored graphically, and through the paired Student’s *t* test as appropriate. Significance will be set at *P* < 0.05. The data will also be modeled within a linear mixed-effects modeling framework to account for repeated measures over time such that between- and within-patient variability can be captured (and estimated). If the modeling provides evidence that sources of variability are significant (e.g., possible relationships between the three readings at each morning and evening), then appropriate adjustments built in to the model will be retained. From such a model, population and individual estimates of treatment means can be obtained, and the influence of additional variables. such as treatment order. can be accounted for (if needed). This statistical analysis will be undertaken in the R package.

The type and severity of possible side effects of the study medication and any serious adverse events will be tabulated for individual patients.

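### The dose rule in Table 2 can take effect between the two halves of a treatment pair, so that one cycle compares the two enalapril products at different doses

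*Protocol article*

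**What the plan says.** Under Selection of doses in the study, patients enter on their existing dose: "They will continue on their current dose for the duration of the trial". The next section, Dose adjustment plan for uncontrolled BP, provides that if control worsens "the dose of enalapril will be adjusted according to a preplanned protocol". Table 2 adds 5 mg when average blood pressure rises by 5 mmHg or more (maximum 25 mg). It removes 5 mg after a fall of 5 mmHg or more with symptoms (maximum shown as 15 mg; no minimum is given). The three rows without adjustment tell the patient to finish the cycle; the two adjustment rows do not.

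Blood pressure is assessed "by a study clinician at the end of each 7-day period" (Trial design, text with Fig. 2), and each pair consists of two such periods, one per product. Eligibility requires that "the enalapril dose is between 5 mg and 20 mg daily", and the abstract describes trial treatment as "each pair comprising 7 days of 5–20 mg local and 7 days of 5–20 mg imported enalapril".

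The cycle is the unit of the equivalence rule. Under Statistical methods, a mean change in evening systolic pressure below 5 mmHg "between the two test medicines in at least two treatment cycles will be considered as representing TE". The section on equivalence criteria also asks for two cycles out of three. The individual result is then handed over so that "the patient and the treating physician will be able to decide if the local drug works" (Individual study result report).

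**The concern.** The design rests on each pair giving a like-for-like comparison within one patient: same patient, same fortnight, same dose, different product. A dose change at the midpoint of a pair breaks this. The cycle difference becomes the product difference plus or minus the effect of 5 mg of enalapril. For a patient who enters on 5 mg, the second product would be taken at twice the dose of the first (10 against 5 mg); for one on 20 mg the ratio is 25/20 = 1.25.

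The article does not say that a change waits for the end of the pair, or that an affected cycle is void or repeated. Cycle replacement appears only under Study withdrawal or interruption, for an interfering concomitant medication. The described analysis does not mention dose. Each patient has only three cycles and needs two of them to count, so one distorted cycle can change the advice that the patient receives.

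**Working it through.** **1. When a change can fall.** There are six 7-day periods in three pairs. Five end-of-period visits precede a further period. Those after periods 1, 3 and 5 lie inside a pair; those after periods 2 and 4 lie between pairs. So three of five visits allow a change that splits a pair.

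**2. Table 2 limits.** From the 20 mg entry ceiling, 20 + 5 = 25 mg and 20 − 5 = 15 mg, which reproduces the table's maxima. At the lower end, 5 − 5 = 0 mg.

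**3. Inputs for size.** The article gives no standard deviation (SD) and no dose effect, so these are assumptions: home period-mean SD 2 mmHg; an extra 5 mg lowers systolic pressure by 2, 3 or 4 mmHg; true systolic pressure N(130, 6); baseline the mean of three visits; triggering pressure SD 3 to 10 mmHg, independent of the home means; at most one upward step; no downward steps. A step needs a rise of at least 5 mmHg and a reading above 140 mmHg. That second condition represents loss of control, using the 140/90 target in the eligibility criteria.

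**4. One cycle.** The observed cycle difference is d ~ N(true ± dose shift, SD 2 × √2 = 2.83), and a cycle passes if |d| < 5.

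| Mean of d (mmHg) | P(pass) | P(5 mmHg or more) |
|---|---|---|
| 0 | 0.923 | 0.077 |
| 2 | 0.849 | 0.151 |
| 3 | 0.758 | 0.242 |
| 4 | 0.637 | 0.363 |
| 6 | 0.362 | 0.638 |

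With identical products, the chance that an affected cycle shows 5 mmHg or more rises from 8% to 15%, 24% or 36% for dose effects 2, 3 and 4.

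**5. Two-of-three rule, equal doses.** P = 3p² − 2p³. With no true difference, p = 0.923 gives 98%. With a true difference of 3 mmHg (inside the margin), p = 0.758 gives 85%.

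**6. Two-of-three rule, one unequal cycle, dose effect 3.** If q is the pass probability in the unequal cycle, P = q[1 − (1 − p)²] + (1 − q)p².
- No true difference: q = 0.758, p = 0.923, so P = 96%.
- True 3, reference at the higher dose: mean 3 + 3 = 6, q = 0.362, p = 0.758, so P = 0.707.
- True 3, test product at the higher dose: mean 3 − 3 = 0, q = 0.923, so P = 0.913.

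A less effective test product triggers the increase more often, and the reference then gets the extra 5 mg. In the simulation the reference had the higher dose in 60–84% of unequal pairs. Weighting gives 0.60 × 0.707 + 0.40 × 0.913 = 0.79 and 0.84 × 0.707 + 0.16 × 0.913 = 0.74, matching the simulated 74–79%.

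**7. Frequency and overall effect** (simulation, 300,000 patients per setting).
- No true difference: 1.3–10.3% of pairs and 4–31% of patients have an unequal pair as the triggering SD goes from 3 to 10.
- True 3, dose effect 3: all-patient passing is 83–84% against 85%.
- Pooled difference over dose effects 2–4: a true 0 stays 0, 3 becomes 3.04–3.10, and 5 becomes 5.08–5.20.

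**8. Changes only between pairs.** No unequal pairs remain, passing returns to 98% (true 0) and 85% (true 3), and the pooled estimates return to 3.00 and 5.00.

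**The case against.** The strongest reply is that Table 2 does not say when a new dose starts. Telling unadjusted patients to finish the cycle may imply that adjusted patients do not simply carry on with theirs. Weekly bottles packed in advance by an independent pharmacy fit that, and a full protocol may contain the dispensing detail. This stands as far as it goes: the text leaves the matter open, and the point is what the printed rule permits, not what was done. But a rule driven by weekly checks, with no deferral stated, is most naturally read as acting at the next weekly bottle. The article prints the rule itself, so this is not merely detail left out.

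A second reply is that the numbers are small and wholly assumed. That is also right for the trial as a whole. The simulation covers only the point-estimate rule under Statistical methods, not the confidence-interval criterion, and it has no downward steps. It does not remove the effect on the patient whose own cycle was distorted.

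Three stronger readings are tempting and are not supported:
- **That the two dose sections flatly contradict each other.** The adjustment plan follows directly and reads as an exception to the fixed-dose sentence.
- **That any chance rise of 5 mmHg changes the dose.** The text first requires that control has worsened, and a decrease requires symptoms. Simulations without a control condition put 17–51% of patients in an unequal pair, but they model a rule that the article does not state.
- **That patients would in practice be taken to 0 mg.** A clinician may withdraw a patient whose "interests are best served by withdrawing from the trial". The missing minimum is a gap in the table, not evidence of a planned zero dose.

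**Conclusion.** The point holds for the affected cycle and the individual report. As printed, the rule allows dose to be confounded with product within a cycle, and nothing shown prevents or repairs this. On the assumptions above it touches about 1–10% of pairs and 4–31% of patients when the products are the same. It lowers two-of-three passing among affected patients from 85% to 74–79% at a true difference and dose effect of 3 mmHg each, and from 98% to 96% when there is no difference.

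A reader might infer that the trial's overall conclusion is unsafe, or that a poor product would be passed. The calculations do not show that. On average the mechanism slightly exaggerates a difference, and pooled movement is 0.1 mmHg or less at a true 3 mmHg. Wrong passing at a true 7 mmHg does not rise even without the 140 mmHg condition (14.5% becomes 14.4% or 12.5%). The actual size and direction cannot be fixed from the article, because it defines neither the baseline for the change in average pressure nor how long an adjusted dose lasts.

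There are three lesser wording points. The fixed-dose sentence should name the exception. The 25 mg maximum does not match the 5–20 mg in the abstract and Table 1. Table 2 has no minimum dose.

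**What to change.** State that dose changes are made only between pairs, so that both products in a pair are taken at the same dose, except where safety needs an immediate change. Name the adjustment as an exception in Selection of doses in the study, give Table 2 a minimum dose, and align the 25 mg maximum with the stated range. Whether to cap at 20 mg is a clinical decision.

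Record the dose taken in each period. Flag any unequal-dose pair in the patient's report, and give individual and pooled results with and without such pairs as a sensitivity analysis. Do not simply drop these pairs from the two-of-three rule. The patient would then need two passes out of two: 0.923² = 85% instead of 96% with no true difference, and 0.758² = 57% instead of 74–79% at a true 3 mmHg. If home pressure is the trigger, dropping also selects on the outcome. In that case (trigger SD 2), the pooled estimate for a true 3 mmHg was 3.13–3.26 with all pairs and 2.82–2.83 without the unequal ones, so reporting both brackets the truth.

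The cost is a short clarification, one dose field per period and one sensitivity analysis. The clinical price is that a non-urgent change may wait up to one week; under the same assumptions 4–31% of patients would meet such a wait at some point when the products do not differ. All 33 patients were enrolled at publication, with completion expected by 7 October 2017. For this trial, therefore, recording, flagging and the sensitivity analysis are the main parts still open; the timing rule matters most for any repeat of the design.

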### Outcome measures

The study physician will assess the patient before and after each treatment period (each week) and collect home BP measurement and Side-effect Recording Forms from the previous week.

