### Safety evaluation and monitoring

Because this is a study of medication that the patient has been taking, the risk of serious adverse events is minimal. All abnormal or unpleasant effects from medications will be considered as side effects. Individual patients will collect common side effects using a questionnaire at home and bring it during their weekly visits. If a patient develops a serious side effect, the study physician will take appropriate measures. The most common side effects of enalapril include increased serum creatinine (20%), dizziness (2–8%), low BP (1–7%), syncope (2%) and dry cough (1–2%). The most serious common AE is angioedema (swelling) (0.68%) which often affects the face and lips, endangering the patient’s airway.

The DSMB consists of two senior members with clinical and methodological expertise who are independent of the trial. They will review all documented harms during the study and adjudicate them with regard to causality.

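### Table 2 row 5, the only row that lowers the dose, has its inequality reversed, and it ties with row 3 at exactly 5 mmHg even when read as intended

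*Protocol article*

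**What the plan says.** Under 'Dose adjustment plan for uncontrolled BP', the protocol article says that doses will be changed by a preplanned scheme, given in Table 2. The first column of the table is the change in average BP. Its five rows are:

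- Row 1: change below +5 mmHg, no adjustment.
- Row 2: change of +5 mmHg or more, "Current dose + 5 mg".
- Row 3: a fall of 5 mmHg or less, no adjustment.
- Row 4: "≥ 5 mmHg fall and asymptomatic", no adjustment.
- Row 5: "≥ − 5 mmHg and symptomatic", dose lowered by 5 mg.

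Rows 1, 2 and 3 set no symptom condition, so they apply with or without symptoms. Row 5 is the only row that lowers the dose. No other section restates or corrects its threshold.

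**The concern.** The table mixes two notations. Rows 1 and 2 use a signed change, rows 3 and 4 describe falls in words, and row 5 returns to a signed number. Row 5 appears to join the 'greater than or equal' of a worded fall to the minus sign of a signed change. The result points the wrong way.

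At stake is the one rule meant to protect a patient whose pressure drops and who feels unwell. Such cases are foreseeable: 'Safety evaluation and monitoring' lists dizziness (2–8%), low BP (1–7%) and syncope (2%) among the common side effects of enalapril. A preplanned dosing rule should not need its user to reverse an operator before applying it.

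**Working it through.** No sample size, power or error-rate figure is involved. The check is which rows apply to a given patient.

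**Inputs, all from Table 2.** Let c be the signed change in average BP, with a rise positive and a fall negative.

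- Row 1: c < 5 if literal, or 0 ≤ c < 5 if read as rises only. No adjustment.
- Row 2: c ≥ 5. Dose +5 mg.
- Row 3: −5 ≤ c ≤ 0. No adjustment.
- Row 4: c ≤ −5 and asymptomatic. No adjustment.
- Row 5: symptomatic, with c ≥ −5 as printed or c ≤ −5 as evidently intended. Dose −5 mg.

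**Symptomatic patient.** The regions below are cut at every row boundary, so the result does not depend on a chosen grid. '0' means no adjustment.

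| Change c (mmHg) | All rows literal | Row 5 literal, row 1 rises only | Row 5 reversed, row 1 rises only |
|---|---|---|---|
| c < −5 | row 1: 0 | no row | row 5: −5 mg |
| c = −5 | rows 1, 3: 0; row 5: −5 mg | row 3: 0; row 5: −5 mg | row 3: 0; row 5: −5 mg |
| −5 < c < 0 | rows 1, 3: 0; row 5: −5 mg | row 3: 0; row 5: −5 mg | row 3: 0 |
| c = 0 | rows 1, 3: 0; row 5: −5 mg | rows 1, 3: 0; row 5: −5 mg | rows 1, 3: 0 |
| 0 < c < 5 | row 1: 0; row 5: −5 mg | row 1: 0; row 5: −5 mg | row 1: 0 |
| c ≥ 5 | row 2: +5 mg; row 5: −5 mg | row 2: +5 mg; row 5: −5 mg | row 2: +5 mg |

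**Results.**

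1. For c < −5 the first two columns differ in form (row 1 applies, or nothing does) but not in effect. Neither lowers the dose. Falls of 6, 10 and 15 mmHg all behave this way.
2. From −5 mmHg upward, row 5 as printed overlaps rows 1, 2 and 3, each time with a different action. For a patient on 10 mg, which is inside the entry range ("the enalapril dose is between 5 mg and 20 mg daily"), a symptomatic 6 mmHg rise gives 10 + 5 = 15 mg by row 2 and 10 − 5 = 5 mg by row 5.
3. The printed condition (c ≥ −5) and the intended one (c ≤ −5) share only the point c = −5.
4. With row 5 reversed and row 1 taken as rises only, one conflict is left, at c = −5: row 3 says no adjustment and row 5 says −5 mg.
5. If row 5 is reversed but row 1 stays literal, row 1 (no adjustment) and row 5 (−5 mg) conflict at every c ≤ −5. Row 1 therefore needs rewording as well.

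**Asymptomatic patient.** Every region gives a single consistent action under all of these readings, so the defect is confined to symptomatic patients.

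**The case against.** The best reply is that nobody would misuse the table. Row 5 follows row 4 directly, replaces asymptomatic with symptomatic, carries a minus sign and lowers the dose. The intended meaning, a fall of at least 5 mmHg with symptoms, is easy to see. That stands, and it limits the weight.

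Two stronger readings are tempting, and the document does not support them.

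- A reader might infer that the table gives no instruction at all for symptomatic falls above 5 mmHg. That holds only if row 1 is read by intent and row 5 by strict arithmetic. Read literally throughout, row 1 applies and gives a wrong instruction, not an absent one.
- A reader might infer that patients with rising pressure risk having their dose cut. The 15 mg versus 5 mg example is a formal contradiction. A physician is unlikely to lower an antihypertensive after a rise when row 2 says to increase it.

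There are also safeguards. The study physician sees patients every week ('Outcome measures'). The article states that "the risk of serious adverse events is minimal" and adds: "If a patient develops a serious side effect, the study physician will take appropriate measures". A clinician may also stop participation when the patient's "interests are best served by withdrawing from the trial". These reduce the possible harm but do not correct the rule.

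The tie at exactly 5 mmHg is narrow, but it survives the most charitable reading of row 5.

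Finally, rewording the conditions settles only which row applies. It does not settle what a 5 mg reduction means for a patient who entered on 5 mg (5 − 5 = 0 mg), nor how Table 2 fits with 'Selection of doses in the study', which keeps patients on their current dose throughout. Those are separate matters.

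**Conclusion.** The point holds as a drafting error in an operative dosing rule. As printed, row 5 does not lower the dose for symptomatic falls larger than 5 mmHg, whichever way row 1 is read, and it formally overlaps rows 1, 2 and 3. Read as intended, one conflict remains, at a symptomatic fall of exactly 5 mmHg.

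The weight is small, because the intent can be inferred from row 4 and physicians have discretion. It is still worth correcting, because the table is the stated basis for changing doses and row 5 is its only reduction. The conclusion assumes that row 5 uses the same signed scale as rows 1 and 2, and that row 4 shows its intended direction.

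A reader might also infer bias in the treatment comparison. Nothing in the document shows how often row 5 would be used or how it was applied, so no effect on the primary estimate is claimed.

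**What to change.** State every condition in words, as a rise or a fall:

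| Row | Condition | Action |
|---|---|---|
| 1 | rise of 0 to < 5 mmHg | no adjustment |
| 2 | rise ≥ 5 mmHg | +5 mg |
| 3 | fall < 5 mmHg | no adjustment |
| 4 | fall ≥ 5 mmHg and asymptomatic | no adjustment |
| 5 | fall ≥ 5 mmHg and symptomatic | −5 mg |

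With an unchanged pressure placed in row 1, exactly one row applies to every patient, with or without symptoms.

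'Trial status' reports 33 patients enrolled, the full planned number, and completion expected by 7 October 2017, three days before the article's publication date. Rewording may therefore come too late to guide conduct. The trial report should say which rule was actually applied to symptomatic falls, including any of exactly 5 mmHg. The cost is a rewritten table and a sentence in the report, with no new visits, measurements or analyses.
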